## Methods

### Study Setting

The Diabetes Belt is a distinct geographic region in the southern United States where county-level adult T2DM rates (≥11%) are especially high and obesity and physical inactivity account for one-third of all diagnosed cases [44]. Mississippi is the only state in which every county (82 counties) is represented by the Diabetes Belt. According to America’s Health Rankings 2019 Report, Mississippi had the third-highest adult T2DM rate (14.3%) in the United States, followed by the second highest adult obesity (39.5%) and physical inactivity (32%) rates [45]. Recent data from the National Survey of Children’s Health (2018-2019) reported in the State of Obesity Report, 2020 [46], identified Mississippi as having the second-highest youth (10-17 years) obesity rate (22.3%) nationally. In addition, AA adults (45.7% [45]) and youth (25.4% [47]) had higher rates of obesity compared with their White counterparts (36.3% [45] and 21.7% [47], respectively). Mississippi also has the highest percentage of Black population (37.8% [48]), and 42% of Mississippi youth are Black compared with 14% nationally [49]. Mississippians experience persistently high rates of poverty (19.7%) and child poverty (27%) [48], and the state is mostly rural and medically underserved [50]; social and environmental factors contribute to poor health and disease. In this context, AA youth in Mississippi are among those at highest risk for T2DM.

The UMMC is the state’s only academic medical center and has the only children’s hospital in the state. In 2019, 4464 AA children aged 8 to 11 years were treated by a UMMC pediatric clinic, and between November 2019 and April 2020, 170 AA children aged 8 to 11 years were identified with the risk for T2DM in the UMMC’s Prediabetes Registry. UMMC is a minority-serving, research-intensive health care organization with a state-mandated requirement to provide not less than 50% of their services to indigent persons (Mississippi Legal Code Annotated 37-115-27; 2017). The UMMC is also a national leader in telehealth [51] and has one of only 2 National Centers of Excellence in Telehealth in the nation [52]. The UMMC Center for Telehealth has successfully intervened with adults with uncontrolled T2DM [53] using remote patient monitoring and is piloting a similar single-arm feasibility trial with pediatric patients (10-17 years) [54]. Health systems with telehealth technology are encouraged to implement and evaluate weight loss interventions for patients at risk for T2DM [32,40,55], and Mississippi is at the forefront of advancing telehealth and adopting mandates for telehealth care reimbursement [51-53,56]. Thus, Mississippi is an ideal location to test the effectiveness and implementation of lifestyle interventions using telehealth in clinical care settings to treat obesity and prevent T2DM in AA youth at the highest risk for diabetes in the United States.

### Participant Recruitment and Sample Size

In-person participant screening and enrollment will be conducted in the UMMC pediatric weight management clinic beginning in December 2020. Preliminary screening will the conducted by the clinical provider using a patient eligibility checklist that will screen for both child and parent eligibility. The lifestyle coach will immediately meet in the clinic room following the clinical encounter to conduct a full screening and provide detailed study information to interested parents and children. Consent forms will be verbally described to parents and children, and parent consent, parent permission, and child assent will be obtained before study enrollment.

Children will be eligible to participate if they are AA, overweight or obese (≥85th percentile for age- and sex-specific BMI), and aged between 8 and 11 years. The child age range was selected to allow for intervention occurring before the average age of youth-onset T2DM, 13 years [10]. The criteria for parents (biological, grandparent, or legal guardian) of eligible children included AA, overweight or obese (BMI ≥25 kg/m^2^), and coresidence with the child. Although mothers represent most participants in family-based studies, we will not use parents’ sex as an inclusion criterion. Parents and children must also be at risk for T2DM based on the following criteria: (1) parents’ T2DM risk will be assessed using the A1CNow^+^ system to measure point-of-care hemoglobin A_1c_ (HbA_1c_), which uses a drop of nonfasting blood (5.7%-6.4%), and the ADA prediabetes screening tool (score ≥5); (2) child risk will be based on the BMI percentile (≥85th percentile) and parents’ risk (BMI ≥25 and ADA screening or HbA_1c_).

Consistent with previous T2DM prevention interventions [26,57], we will exclude families if the child or parent has a history of T2DM or a screening HbA_1c_ level greater than 6.4%, is taking glucose-lowering medications, is participating in a supervised weight loss program, is pregnant or breastfeeding, has conditions limiting participation, has undergone weight loss surgery, or is moving out of state within 6 months. If a parent becomes pregnant during the study, we will include only child data (index participant) in the analyses. Technology literacy will not be included as an exclusion criterion. Participants will receive technology instruction from the telehealth center and be provided technical support as needed.

The power calculation, across 5 scenarios, shows detectable effect sizes, ≥−2.5 (SD 0.05) BMI in parents [58] and in children, where a modest reduction in BMI z score (≥0 to <−0.1, SD 0.05) has been associated with improved cardiometabolic risk [59]. In the first 3 scenarios, assuming 10% attrition [37], a minimum of 18 dyads are needed. In scenarios 4 and 5, detectable effect sizes are reported in the case of 0% (n=20 dyads) and 20% (n=16 dyads) attrition. We anticipate 20% attrition, which is consistent with the group- and family-based telehealth lifestyle intervention literature [60-62]. Analyses are based on α=.05 and a conservative two-sided test. An effect size of 1.0 is considered substantial and 0.5 is considered medium. We will obtain reliable effect size estimates to design a pilot randomized controlled trial.

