### Objectives

The Telehealth Diabetes Prevention Intervention for the Next Generation of African American Youth (TELE-GEN) pilot trial proposes implementing and evaluating a diabetes prevention intervention based on the *Power to Prevent* program for AA parents of children (8-11 years) who are both overweight or obese and at risk for T2DM. Historically, a lengthy effectiveness study conducted under *ideal circumstances* would be the next step in identifying a gold standard lifestyle intervention to prevent T2DM in AA youth; however, standard effectiveness studies are limited by their inability for rapid translation and the need for subsequent implementation studies to validate utility in real-world settings [43]. Hybrid research designs leverage the rigor of clinical trials and implementation science to foster rapid translation and effective implementation [33,43]. Thus, in partnership with the Center for Telehealth at the University of Mississippi Medical Center (UMMC) and pediatric weight management clinic, we propose a novel effectiveness-implementation hybrid type II research design [43] with the coprimary aim to (1) conduct a 30-week, single-arm pilot trial with at-risk parents of at-risk children to assess the early efficacy of Power to Prevent delivered using small group-based videoconferencing to reduce BMI in parents (n=20) and stabilize or reduce BMI z scores in children (n=20), while (2) conducting a comprehensive evaluation of a multifaceted implementation strategy for the uptake of the intervention by the pediatric weight management clinic at the UMMC in Jackson, Mississippi. The protocol described below was approved by the UMMC’s Institutional Review Board (#2020V0249).

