#### Intervention Participant Retention

Telehealth is an effective retention strategy used in the DPP [86] and mitigates transportation barriers [87]. The lifestyle coach will dedicate time outside of intervention sessions to build rapport with parents and will function as a personal contact for participants to establish meaningful relationships, send meeting reminders, and schedule and conduct make-up sessions (consistent with DPP [63]) [86]. Participants will be incentivized using attendance raffles for cooking (eg, measuring cups), physical activity equipment (eg, jump rope), and incremental monetary compensation at each assessment point (baseline, US $50; postintervention, US $75; follow-up, US $150) [86]. Study assessments will be conducted in-person at the time of the child’s routine appointment with the pediatric weight management clinic and monetary resources will be allocated to families experiencing transportation barriers.

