#### Intervention Efficacy Measures

Primary and secondary outcome measures will be assessed at baseline (week 1), postintervention (week 12), and 4-month follow-up (week 30). The primary outcome measure will be a reduction or stabilization in the child BMI *z* score (index participant) and a reduction in parent BMI (coparticipant) [88]. Secondary outcomes include anthropometric (waist circumference and body composition), biomarker (HbA_1c_, blood pressure, resting heart rate, lipid profile, and Tanner stage), behavioral (fruit and vegetable, sugar-sweetened beverage, and sweat and salty snack consumption; family meal frequency; fast food meal frequency; physical activity volume; and sedentary time), psychosocial (self-efficacy, self-regulation, readiness to change, family functioning, and perceived stress), and environmental (home food and physical activity environment and perceived neighborhood support for healthy eating and physical activity) measures (Table 1). All the measurements will be recorded electronically using REDCap (Research Electronic Data Capture) tools hosted at the UMMC [89]. REDCap is a secure, web-based software platform designed to support data capture for research studies, providing an intuitive interface for validated data capture; audit trails for tracking data manipulation and export procedures; automated export procedures for seamless data downloads to common statistical packages; and procedures for data integration and interoperability with external sources.

**Table 1 table1:** Pilot trial outcome measures.

Outcome measure and instrument				Participant

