### Data Analysis

Participant sociodemographic characteristics at baseline will be described using means and SDs, medians and ranges, or frequencies with percentages where applicable. The primary outcome evaluation will assess the change in child BMI *z* score (index participant) and parent BMI (coparticipant) from baseline to 12 and 30 weeks using repeated measures analysis of covariance with child Tanner stage as the covariate. Secondary analyses will include the comparison of anthropometric, biomarker, behavioral, psychosocial, and environmental measures adjusted for other factors. Generalized linear modeling will be used to assess the effect of the intervention, both unadjusted and adjusted (controlling for demographics, baseline BMI *z* score, and BMI). Data will be analyzed according to intention-to-treat principles [106-108].

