## Results

Recruitment and enrollment began in December 2020, and the first cohort of families will begin the intervention in March 2021. As of March 15, 2021, 10 children and their parents were enrolled in the study; however, intervention delivery had not begun. Future outcomes will be published in peer-reviewed health-related research journals and presented at national, regional, or state professional meetings and conferences. Preliminary findings will position the investigative team to design a subsequent hybrid study that will include a powered pilot randomized controlled trial with a larger sample of families and providers, a usual care control arm, and long-term follow-up; a robust evaluation of a refined implementation protocol; and cost-benefit and return-on-investment analyses.

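### The 6-month relocation exclusion is shorter than the 30-week trial, so a family known to be leaving the state before the in-person week-30 primary visit is eligible

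*Protocol article*

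**What the plan says.** All references are to the Protocol article.

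- **Relocation rule.** Participant Recruitment and Sample Size lists reasons for excluding a family if they apply to the child or the parent. The last reads "or is moving out of state within 6 months". The text does not say whether the six months run from screening, enrollment or the first session.
- **Length.** Objectives commits to "conduct a 30-week, single-arm pilot trial".
- **Primary time points.** Intervention Efficacy Measures places assessments at weeks 1, 12 and 30. Data Analysis evaluates change in child BMI z score and parent BMI "from baseline to 12 and 30 weeks using repeated measures analysis of covariance".
- **Mode of measurement.** Intervention Participant Retention states: "Study assessments will be conducted in-person", timed to the child's routine clinic appointment. Money is set aside for families with transportation barriers. No remote measurement is described.
- **Time between enrollment and start.** Recruitment is described as follows: "In-person participant screening and enrollment will be conducted in the UMMC pediatric weight management clinic beginning in December 2020". The first cohort was to start in March 2021. Results adds: "As of March 15, 2021, 10 children and their parents were enrolled in the study; however, intervention delivery had not begun".

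**The concern.** An exclusion for planned relocation is most naturally read as protecting follow-up, and here it stops short of the last primary visit. No other criterion asks for availability through week 30. The general exclusion for conditions that limit taking part could be stretched to cover a planned move, but relocation has its own criterion, which argues against that reading.

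What is at stake is foreseeable loss of week-30 primary data in a trial of 20 dyads. Retention is also one of the feasibility dimensions in Evaluation Measures. A dyad lost to a move already known at screening lowers that figure for a reason unrelated to the intervention.

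**Working it through.** **Inputs.** Exclusion window 6 months; trial 30 weeks; visits at weeks 1, 12 and 30; enrollment from December 2020; first cohort starting in March 2021; 20 dyads; anticipated attrition 20%. One month is taken as 365.25/12 = 30.44 days.

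**1. The plan's own schedule.** The last visit is called a 4-month follow-up after week 12. 12 + 4 × 30.44/7 = 29.4 weeks, which agrees with week 30. Eleven weekly and four monthly sessions take 11 + 17.4 = 28.4 weeks, which also fits. The 30-week figure is sound.

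**2. Both durations in one unit.** Window: 6 × 30.44/7 = 26.1 weeks. Trial: 30 × 7/30.44 = 6.9 months.

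**3. Gap with no wait, or with the window counted from session 1.** Baseline is labelled week 1, so week 30 may mean 29 or 30 elapsed weeks.
- 29 − 26.1 = 2.9 weeks
- 30 − 26.1 = 3.9 weeks

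**4. Gap if the window runs from screening.** Gap = wait + 29 (or 30) − 26.1, taking a December 2020 enrollment and a March 2021 start.
- Shortest wait, 31 December to 1 March: 60 days = 8.6 weeks. Week 30 falls from 8.6 + 29 = 37.6 weeks after enrollment; gap 11.5 weeks.
- Longest wait, 1 December to 31 March: 120 days = 17.1 weeks. Week 30 falls up to 17.1 + 30 = 47.1 weeks after enrollment; gap 21.1 weeks (unrounded inputs).
- Results says nothing had been delivered by 15 March. With that as the earliest start, the lower end becomes 74 days = 10.6 weeks of waiting and a gap of 13.5 weeks.
- A family enrolled in March shortly before its group started would be close to the 3 to 4 weeks of step 3.

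**5. Week 12.** For the same December enrollees, wait + 12 runs from 20.6 to 29.1 weeks. It passes 26.1 weeks only for the longest waits: enrolled about 1 December, it is 26.9 weeks with a 15 March start and 29.1 with a 31 March start. Week 12 is normally inside the window.

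**6. Weight of one dyad.** 1/20 = 5% of the sample. Anticipated loss is 20 × 0.20 = 4 dyads, so one dyad is a quarter of it.

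**7. Expected number affected.** The documents give no relocation rate. As an assumption only, let 1% to 5% of families a year have a planned interstate move. Expected dyads = 20 × rate × gap/52.
- Gap of 4 weeks: 20 × 0.01 × 4/52 = 0.02 to 20 × 0.05 × 4/52 = 0.08
- Gap of 21 weeks applied to all 20 dyads: 20 × 0.01 × 21/52 = 0.08 to 20 × 0.05 × 21/52 = 0.40

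Under this assumption the expected loss is below one dyad in every case.

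**The case against.** The strongest reply is that this hardly matters. A loss needs a family that already plans, at screening, to leave the state in a narrow interval. Week 12 is usually kept. The plan anticipates 20% attrition and reports detectable effects at 16 dyads. Sessions are by video on cellular-enabled iPads, so a family that moves can stay in the intervention. Transport money and the follow-up payment make a return visit unlikely rather than impossible. Interviews and outreach records could show that a loss was due to relocation. All of this stands and limits the size of the point. None of it closes the gap between 26 and 30 weeks.

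A reader might also infer that the rule misses the trial by more than four months: from 1 December to 15 March is 104 days, and 104 + 210 = 314 days, or 10.3 months. The documents do not establish this. It needs a window that starts at screening, which is not stated, and enrollment on the first possible day, when no individual dates are given. If baseline is taken at enrollment, week 30 is only 3 to 4 weeks past the window, although the sessions would then not match the week-12 and week-30 labels for families who waited.

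Finally, the purpose of the rule is an inference. The article presents its exclusions only as consistent with previous prevention trials.

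**Conclusion.** The mismatch is real and stands in the stated text: a 26-week window against a 30-week trial with an in-person primary visit at week 30. The gap is 3 to 4 weeks on the most favorable reading. It is roughly 11 to 21 weeks for December 2020 enrollees starting in March 2021 if the window runs from screening. The first figure needs only the stated durations; the second rests on an unstated start of the window and unknown enrollment dates.

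The documents do not support a claim that primary data will be materially depleted. Week 30 is one of two primary time points, and the number of affected dyads is unknown and probably below one. Nor do they support replacing dyads already enrolled because they are expected to miss week 30. That would sit badly with the intention-to-treat statement in Data Analysis and would flatter the retention figure. This is a minor point, worth correcting because the correction is cheap.

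**What to change.** For families not yet enrolled, word the exclusion as planning to move out of state before the family's expected week-30 assessment, counted from the planned start of their group. Put the same question, with the expected date, on the screening checklist. This also removes the doubt about when the window starts.

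Do not replace dyads already enrolled (10 at 15 March 2021). Keep them in the intention-to-treat set and record relocation as the reason for any missed visit, so that the retention result can be read correctly.

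The cost is one line of eligibility wording and the checklist, presumably through a minor amendment because the protocol has ethics approval, and a few more families screened out.

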	**Home physical and social environment**			
		Modified Home PA and Food Environment Scale, 100 items (Gattshall et al [97]); subscales: availability and accessibility of food, physical activity equipment, and technology devices; parent role modeling and family policies for food, physical activity, and technology use	Parent	

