**Behavioral measures**				
	**Child behavior (subjective)**			
		Child Obesity Behavior Questionnaire; 20 items to measure parents’ perception of the child’s dietary, physical activity, and sedentary behaviors (Rhee et al [98])	Parent	
		Healthy Eating and Physical Activity Recall Questionnaire, 9 items (Lassetter et al [96]), modified to assess technology environment, and 5 items	Child	

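### The pregnancy rule, read as written, drops a parent's valid pre-pregnancy BMI and questionnaire data and sits badly with the intention-to-treat statement; the likely effect is small and the fix is cheap

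*Protocol article*

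**What the plan says.** Under Participant Recruitment and Sample Size, the article has two separate pregnancy provisions. The first is a screening exclusion for a child or parent who "is pregnant or breastfeeding, has conditions limiting participation", among other reasons. The second applies after enrolment: "If a parent becomes pregnant during the study, we will include only child data (index participant) in the analyses". The second sets no limit on which visits, measures or analyses it covers.

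Intervention Efficacy Measures makes parent BMI part of the primary outcome, alongside the child BMI z score: "index participant) and a reduction in parent BMI (coparticipant". Outcomes are "assessed at baseline (week 1), postintervention (week 12), and 4-month follow-up (week 30". The efficacy Data Analysis section evaluates the change in both from baseline to 12 and to 30 weeks by repeated measures analysis of covariance, and adds: "Data will be analyzed according to intention-to-treat principles". No exception for pregnancy is stated there.

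Table 1 names the parent as the participant for several instruments unrelated to body weight. Among them are parental self-efficacy, family functioning, perceived stress and the home environment scale, whose subscales include "parent role modeling and family policies for food, physical activity, and technology use".

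**The concern.** Pregnancy invalidates BMI as a measure of the intervention's effect on weight, so leaving out BMI measured during pregnancy is reasonable. The difficulty is how far the sentence reaches. It takes a post-enrolment event and, on its plain wording, removes the whole parent record, including measurements taken before the event.

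Two things are at stake. The week-12 change in parent BMI is one of the two parent primary contrasts, and it would lose usable values in a trial of only 20 parents. The child would also stay in the analysis without the parent-reported home, motivation and family-functioning data, which the Conceptual Model section treats as part of how the intervention is meant to work.

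The rule also selects the analysis set on something that happens after baseline, while another section promises intention to treat without qualification.

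**Working it through.** **1. The sample.** From Participant Recruitment and Sample Size: 20 dyads enrolled, 18 at 10% attrition, 16 at 20% attrition (the level anticipated). Check: 20 × (1 − 0.10) = 18 and 20 × (1 − 0.20) = 16. The stated counts reproduce.

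**2. Weight of one parent.** 1/18 = 5.6%; 1/16 = 6.3%.

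**3. What the rule removes and what could be kept, by time of conception.**

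| Conception | Parent BMI unaffected by pregnancy | Kept under the rule as written | Kept if only affected post-conception measures are excluded |
|---|---|---|---|
| After the week-12 visit | Baseline and week 12 | None | Baseline and week 12 |
| Between baseline and week 12 | Baseline | None | Baseline |

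The week-30 BMI of a parent pregnant at that visit is unusable either way. The recoverable primary-outcome information is therefore mainly the week-12 change of parents who conceive after week 12. Parent questionnaires are recoverable in both rows.

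**4. Effect on precision.** The article states a two-sided α of .05 but no power; 80% and 90% are assumed here. For a one-sample t test on change with n parents and standardized change d, power = P(T > t₀.₉₇₅,ₙ₋₁), where T is noncentral t with n − 1 degrees of freedom and noncentrality d√n. The number of pregnancies is not given; 0 to 3 among the 16 expected completers is assumed.

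| Pregnancies | n | Detectable d, 80% power | Detectable d, 90% power | Power at d = 0.5 |
|---|---|---|---|---|
| 0 | 16 | 0.75 | 0.87 | 46.5% |
| 1 | 15 | 0.78 | 0.90 | 43.8% |
| 2 | 14 | 0.81 | 0.94 | 41.0% |
| 3 | 13 | 0.85 | 0.98 | 38.2% |

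One lost parent moves the detectable change at 80% power by 0.78 − 0.75 = 0.03 and lowers power at d = 0.5 by 46.5 − 43.8 = 2.7 percentage points.

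**5. The two statements side by side.** The trial has one arm, so intention to treat cannot be about protecting a randomized comparison. What it can still mean is that enrolled participants remain in the analysis set. A rule that takes an enrolled parent out of every analysis, including measurements made before she conceived, departs from that, and the analysis section does not acknowledge the departure.

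**The case against.** The strongest reply is that this is one sentence in the recruitment section of a journal article. It never says that pre-pregnancy BMI or questionnaires are deleted, and a full protocol or analysis plan could narrow it. That lowers the certainty about what will be done. It does not remove the point, because the article does not leave the matter open: it states a rule, and the rule as stated is the broad one.

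Several stronger readings are tempting but not supported:

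- **That the rule is the reverse of intention to treat.** This goes too far. It is a single-arm pilot, the exclusion is declared in advance, and it is tied to an event that confounds the weight outcome. The two passages could be read as a principle with one declared exception. What stands is that the analysis section does not say so.
- **That the child's behavior data are lost.** The parent-completed instrument, "20 items to measure parents’ perception of the child’s dietary, physical activity, and sedentary behaviors", is filed in Table 1 under child behavior. The parent entry may only name the respondent, so it may already count as child data. The child also completes a recall questionnaire and wears an accelerometer.
- **That most pregnancies would fall after week 12.** Weeks 13 to 30 are 18 of 30 study weeks (60%), but that is a share of the calendar. It is neither a probability of pregnancy nor a fraction of data lost.
- **That many parents will be affected.** The article notes: "Although mothers represent most participants in family-based studies, we will not use parents’ sex as an inclusion criterion". Grandparents and legal guardians of either sex are also eligible, which lowers the expected number.

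One practical objection also stands. If the repeated measures analysis is run on complete cases only (the article does not say), a parent whose week-30 BMI is set to missing drops out anyway. Rewording the rule alone would then not recover her week-12 value.

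**Conclusion.** The point holds in a limited form. As worded, the rule discards parent BMI values that pregnancy has not touched, together with parent questionnaires, and it is not reconciled with the unqualified intention-to-treat statement.

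The size is probably small. With no pregnancies there is no loss. With one, 5.6% to 6.3% of the analysed parents go, and the detectable standardized change at 80% power moves from 0.75 to 0.78. The child primary outcome is unaffected.

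This rests on reading the sentence without limits that it does not contain, on an assumed 0 to 3 pregnancies, and on assumed power. It is worth correcting because the sample is small, the values are valid, and the correction costs little; the trial's conclusions do not depend on it.

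**What to change.** Restrict the exclusion and carry it through to the analysis:

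1. Exclude only parent measures that pregnancy affects and that are taken after estimated conception: BMI, body composition and waist circumference, and also HbA1c, lipids, blood pressure, resting heart rate and accelerometry.
2. Retain all earlier parent measurements, and retain the parent questionnaire and implementation data throughout. State that the parent-completed child behavior questionnaire counts as child data.
3. Fit the primary parent BMI analysis with a method that uses every available visit, such as a likelihood-based mixed model, so that a missing week-30 value does not remove the week-12 value.
4. Report full exclusion of these parents as a sensitivity analysis.
5. Put this in the efficacy Data Analysis section as the declared handling of pregnancy under the intention-to-treat statement, and make the recruitment section agree with it.

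The cost is one added data item (estimated conception date), one extra sensitivity analysis and revised wording. No extra visits are needed.

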**Methods:**

This single-arm trial will enroll 20 parents with overweight or obesity of children (8-11 years) with overweight or obesity, both of whom are at risk for T2DM. Parents will meet in small groups (5 parents per group) weekly for 11 weeks and then monthly for 4 monthly maintenance sessions via videoconference using Wi-Fi–enabled iPads with cellular connectivity. The intervention will be adapted from the National Diabetes Prevention Program and *Power to Prevent*, a diabetes prevention program tailored for AA families. The same lifestyle intervention facilitated by a racially concordant lifestyle coach trained in the Diabetes Prevention Program will be delivered to all groups (n=4). Participants will be recruited in-person during patient encounters at the UMMC’s pediatric weight management clinic. Sessions will consist of dietary and physical activity behavior change strategies facilitated using problem-solving and goal-setting skills. The implementation strategy has 2 targets: the pediatric weight management clinic site and clinical team and parents of children at risk for T2DM engaged in intensive obesity treatment to prevent T2DM. The multifaceted implementation protocol includes 4 discrete strategies: creating a new clinical team, changing the service site, intervening with families, and promoting organizational readiness for change.

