### Intervention

Power to Prevent [28] is a diabetes prevention intervention based on the DPP [63] and the *Small Steps, Big Rewards Program* [69] and is tailored for AA families. The goal of the program is to achieve a 5% to 7% weight loss by making modifications to dietary, physical activity, and sedentary behaviors. In the proposed pilot trial, modification to family dietary, physical activity (≥150 min per week), and sedentary behaviors will be targeted, in addition to individual-level parent behaviors. The *Power to Prevent*
*Leader Guide* and participant materials will be adapted and used in each session. The scientific literature strongly supports family-based approaches to treating youth with overweight or obesity [70]. Thus, group-based sessions (60 min) will be conducted with parents and target the adoption, maintenance, and self-regulation of family-focused dietary, physical activity, and sedentary behaviors. Parent participants will meet weekly for 11 weeks and then monthly for 4 pilot maintenance sessions (15 sessions in total; frequency and duration supported by the literature [71]). Sessions for all groups will be facilitated by a racially concordant lifestyle coach (interventionist) who will be trained in accordance with the Centers for Disease Control and Prevention Diabetes Prevention Recognition Program standards [72]. Wi-Fi–equipped iPads (12.9”) with cellular connectivity will be used to link families to videoconferencing sessions and to cooking and family-friendly physical activity video demonstrations via YouTube.

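### The SD of 0.05 printed for parent BMI makes the −2.5 change an effect of 50 SD, and the required 18 dyads is recovered only as 20 less 10% attrition

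*Protocol article*

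**What the plan says.** All of this is in the protocol article, Participant Recruitment and Sample Size, unless noted.

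- Parent outcome: the power calculation "shows detectable effect sizes, ≥−2.5 (SD 0.05) BMI in parents [58".
- Child outcome: "a modest reduction in BMI z score (≥0 to <−0.1, SD 0.05" is described as associated with improved cardiometabolic risk.
- Number needed: the first three of five scenarios assume 10% attrition and are said to require at least 18 dyads. Scenarios 4 and 5 give detectable effects at 20 dyads (0% attrition) and 16 dyads (20% attrition). The paragraph anticipates 20% attrition.
- Test: "Analyses are based on α=.05 and a conservative two-sided test".
- Scale: "An effect size of 1.0 is considered substantial and 0.5 is considered medium".
- Design (Abstract, Methods): "This single-arm trial will enroll 20 parents with overweight or obesity of children (8-11 years", so the effect of interest is a within-person change.

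**The concern.** Parent BMI is in kg/m² and child BMI z is in growth-reference SD units. The same SD of 0.05 is unlikely to suit both, and for parents it produces an effect far off the paragraph's own scale. This suggests that a design input was miscopied.

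The number 18 is presented as a requirement, so a reader will look for the effect and SD that produce it. If the printed inputs do not lead there, the only sample-size justification in the article does not support its figure. The wording also matters in itself: if 18 really were a minimum, the anticipated 20% attrition would leave 16 and the trial would be expected to fall short of its own requirement.

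**Working it through.** **Inputs from the article.** Single arm; 20 dyads enrolled; two-sided α=.05; parent change 2.5 in magnitude with SD 0.05; child range bounded by 0.1 z with SD 0.05; benchmarks 1.0 and 0.5; n = 20, 18 and 16.

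**Assumptions.** Power of 80% and 90%, because the article gives none; the printed SDs taken as SDs of within-person change; a simple paired t test.

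**Formula.** With d = change / SD, power at n is P(|T| > t(0.975, n−1)), where T is noncentral t with n−1 degrees of freedom and noncentrality d√n. The required n is the smallest that reaches the target.

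**1. The plan's own figure.** 20 × (1 − 0.10) = 18 and 20 × (1 − 0.20) = 16. Both are recovered as counts of completers.

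**2. Parents, as printed.** d = 2.5/0.05 = 50. Required n = 2 at either power (simulated power at n=2 was 1.0). For 18 to be the requirement for a change of 2.5, the SD of change would have to be 2.5/0.701 = 3.57 (80%) or 2.5/0.811 = 3.08 (90%), not 0.05.

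**3. Benchmarks.**

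| d | n at 80% power | n at 90% power |
|---|---|---|
| 1.0 | 10 | 13 |
| 0.5 | 34 | 44 |

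With one-sided 0.05, one-sided 0.025 or two-sided 0.025 instead, d = 1.0 needs between 8 and 16, and d = 0.5 between 27 and 53. None of these gives 18.

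**4. Child, as printed.** Literally, no number is both at least 0 and below −0.1. Read as a reduction between 0 and 0.1, the upper bound gives d = 0.1/0.05 = 2, which needs 5 children (power 0.755 at n=4, 0.909 at n=5). A smaller reduction in the same range gives 18: 0.701 × 0.05 = 0.035 z at 80%, or 0.811 × 0.05 = 0.041 z at 90%. The article names neither value.

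**5. What the planned sizes can detect.**

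| n | detectable d, 80% power | detectable d, 90% power | power at d = 0.5 |
|---|---|---|---|
| 16 | 0.75 | 0.87 | 46% |
| 18 | 0.70 | 0.81 | 52% |
| 20 | 0.66 | 0.76 | 56% |

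**The case against.** The strongest defence is that this is a condensed account of a pilot. The paragraph reports detectable effects at fixed sizes; 16, 18 and 20 are 20 dyads under three attrition rates; the power level and the inputs of the five scenarios may sit in the full protocol. That much stands, and the missing power level is not part of this point. Condensing does not, however, explain an SD of 0.05 for BMI in kg/m², nor turn a count of completers into a required minimum.

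Several stronger readings are tempting, but the document does not support them.

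- *The child inputs need only 5 dyads, so they contradict 18.* The 0.1 z figure bounds a range of clinical relevance and is not stated as the design effect. A change of about 0.035 z at SD 0.05 would give 18.
- *The child range is meaningless.* The words describing a modest reduction make the intended range readable. This is a sign slip.
- *The parent change exceeds the program's own aim* (Intervention: "The goal of the program is to achieve a 5% to 7% weight loss"). A 7% loss equals 2.5 kg/m² at BMI 35.7 (0.07 × 35.7 = 2.5) and a 5% loss at BMI 50 (0.05 × 50 = 2.5). How many parents lie below those values needs a BMI distribution that the article does not give; it states only entry at BMI 25 or more. A program goal and a detectable effect also need not agree.
- *The trial is underpowered for a 0.1 z change.* That depends on an SD of change the article does not supply beyond the doubtful 0.05.

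It is also fair to say that the planned primary analysis is a repeated measures analysis of covariance (Data Analysis), not a paired t test. The t test figures are therefore a reference calculation. A change of test would not make an effect of 50 SD plausible.

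**Conclusion.** The point holds for the parent figure and for the wording around 18. An effect of 50 SD is incompatible with a scale on which 1.0 is substantial. On the printed parent inputs 2 participants would suffice. Neither benchmark leads to 18 under a single-arm test, and the number is traceable only to 20 less 10% attrition. These conclusions are the same at 80% and 90% power.

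For the child outcome the conclusion is weaker: the sign is wrong and no design effect is fixed, but SD 0.05 does not by itself conflict with 18.

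The detectable changes of about 0.75, 0.70 and 0.66, and the power of about 46% to 56% for a medium effect, rest on the paired t test, with 80% power also assumed for the former. The error lies in the stated justification. It does not show that 20 dyads is the wrong size for a pilot.

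**What to change.** Rewrite the paragraph as follows.

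1. Correct the parent SD, and confirm or correct the child SD, giving each as the SD of within-person change for that outcome.
2. Correct the sign of the child range so that it reads as a reduction.
3. Describe 18 as the number of dyads expected to complete at 10% attrition, alongside 16 at 20% and 20 at 0%, and drop the claim that it is a required minimum.
4. State the sensitivity as detectable standardized changes: about 0.75, 0.70 and 0.66 at n=16, 18 and 20, labelled as assuming 80% power and a simple paired t test (or the team's own figures if the full calculation used another power or test). Convert them to kg/m² and z units with the corrected SDs.
5. Add that, under the same test, a medium effect of 0.5 has about 46% to 56% power at these sizes.

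The cost is one reworded paragraph and a less favourable stated sensitivity. The number enrolled, the design and the analysis do not change.
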